**Figure 2 F2:**
[figure not shown]
Study design.

Both process and impact evaluations will be carried out using mixed methods. Primary and secondary nutrition outcomes include longitudinal difference-in-difference analyses of parameters – height-for-age *Z* score, stunting prevalence, child fish food intake, child dietary diversity, and child diarrheal morbidity. Other outcomes include awareness of the social marketing campaign and knowledge transfer. Primary and secondary fisheries outcomes will be longitudinal difference-in-difference analyses in fisheries yield of mature fish and fisher income and earnings.

The *Samaki Salama* intervention precludes randomization due to the high risk of spill-over effects and the limited number of trap fishers with children under the age of 5. Thus, for the impact assessment, we will conduct a matched intervention/control design to minimize selection bias and test effectiveness on nutrition and fisheries production. Steps have been taken to reduce the risk of selection bias that might arise from the matched design. A pilot study and additional formative research will be used to identify and match communities on important characteristics [socioeconomic status (SES), child nutrition, livelihoods, etc.]. This preliminary data provides additional information needed for external validity and extrapolation of findings to other small fisher households in Kenya and internationally. The longitudinal difference-in-difference design further contributes to the internal validity, accounting for residual confounding, and increases the statistical power to detect intervention effects.

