### Sample size

Sample size calculations for the cluster design applied a mean −1.3 height-for-age (HAZ) for the coast region (20) and a hypothesized 0.20 effect size (21). Thus, we estimate requiring a total sample size of 400 households, which includes ~4 clusters per arm (four villages per BMU) and 50–75 households per cluster – assuming 20% losses-to-follow-up (α = 0.05 and 1-β = 0.80). Although this is small number of clusters, we will apply matching techniques a priori and during data analyses (e.g., propensity score matching) to better ensure internal validity.

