### Analysis

#### Primary and secondary outcomes

Generalized linear regression modeling (GLM), allowing for non-normal distributions, will test the continuous outcomes of HAZ, WAZ, child dietary fish intake, child dietary diversity score, fisheries yield, and fish earnings. As a difference-in-difference analyses, change variables for each outcome will be examined (difference between baseline and endline). For the binomial outcomes of diarrhea morbidity (and other outcomes of stunting and underweight), we will estimate prevalence ratios by the GLM modeling with robust Poisson. If stunting prevalence in this population exceeds the acceptable threshold for use of odds ratios (0.2105), prevalence ratios (PRs) will be used to examine the intervention effect and were considered analogous to relative risk in this longitudinal study. The robust Poisson, with a classic sandwich estimator to correct the inflated variance of standard Poisson, is less affected by outliers.

To test for intervention effectiveness, the two intervention groups will be combined for all hypotheses except the secondary outcome of increased fisher earnings and exploratory hypothesis for differences between social marketing and social marketing + traps intervention groups. Regression models will be adjusted for potential confounding factors including age, sex of the child, corresponding baseline measures, and others found to differ significantly between the trial groups (e.g., maternal education). For fisheries yield, confounding factors will be used to adjust regression models, such as: water temperature, fishing ground area, coral cover, and seasonality. The *P* significance value for Type I error (and one-tailed test) will be *P* < 0.05 and corresponding 95% confidence interval. Diagnostics for regression model assumptions, structure and observations will be applied, and corrective procedures applied as necessary. If selection bias is widely detected with important differences across intervention and control communities, we will apply propensity score analyses (36). Data analyses will be performed with Stata software (version 16.0; StataCorp, College Station, TX) and R (4.1.2).

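### For the continuous nutrition outcomes, the model called difference-in-difference adjusts for its own baseline; it is ANCOVA and lacks the protection against confounding that the Design section claims

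*Protocol article*

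**What the plan says.** The Design section of the protocol article explains that the "intervention precludes randomization due to the high risk of spill-over effects" and the small number of eligible trap fishers, and chooses matched communities instead. It names longitudinal difference-in-difference analyses for both the nutrition and the fisheries outcomes, and gives that choice a specific job: "The longitudinal difference-in-difference design further contributes to the internal validity, accounting for residual confounding".

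The Analysis section (Primary and secondary outcomes) sets out the model. The outcome is a change score: "As a difference-in-difference analyses, change variables for each outcome will be examined (difference between baseline and endline". The next paragraph adds the covariates: "Regression models will be adjusted for potential confounding factors including age, sex of the child, corresponding baseline measures", plus other factors that differ between groups. Nothing exempts the change-score models for the nutrition outcomes from the baseline covariate.

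The same section adds a conditional safeguard: "If selection bias is widely detected with important differences across intervention and control communities, we will apply propensity score analyses". The Sample size section refers to matching both beforehand and at the analysis stage, with propensity score matching as its example. Study measures and Table 5 give two timepoints, baseline and 12 months, for growth, fish intake and dietary diversity.

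**The concern.** DiD and ANCOVA answer the confounding problem under different assumptions. DiD subtracts each group's own starting level, so a fixed difference between communities drops out if both groups would otherwise have moved in parallel. ANCOVA compares children with the same measured baseline, so it needs the groups to be comparable once that baseline is known. Adding the outcome's own baseline to a change-score model turns the first into the second.

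In a randomised trial the expected baseline gap is zero and the two agree on average. Here communities are assigned, there are about four clusters per arm, and the protocol relies on DiD by name. The stated model does not have the property claimed for it, and the two models can give different answers from the same data. Because the Analysis section specifies a one-tailed test, an upward error would feed directly into false positive findings.

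**Working it through.** **Inputs from the protocol.** Change score as outcome and its own baseline as covariate (Analysis); assigned communities and the DiD claim (Design); HAZ target, "a hypothesized 0.20 effect size" (Sample size); WAZ target 0.10 (Table 1); 400 households, 20% loss (Sample size), hence 200 × 0.8 = 160 per group for combined intervention against control.

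**Inputs that are assumptions.** The protocol gives no baseline gap, outcome SD, intraclass correlation (ICC) or baseline–endline correlation. It therefore offers no figure of its own to reproduce on this point. An identity link is also assumed.

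**Step 1: the planned model is ANCOVA.** Let G be group, Y0 baseline and Y1 endline. The planned model is

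Y1 − Y0 = a + t·G + c·Y0.

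Adding Y0 to both sides gives

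Y1 = a + t·G + (1 + c)·Y0.

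The group coefficient t is the same in both. In simulation the two estimates agreed to 0.000 in every setting.

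**Step 2: relation to DiD.** Write b = 1 + c, and gap for the baseline mean of the intervention group minus that of control. Then

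t = (endline difference) − b × gap, and DiD = (endline difference) − gap,

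so t = DiD + (1 − b) × gap. With age, sex and other covariates in both models, the relation holds with the covariate-adjusted gap.

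**Step 3: size under parallel trends.** DiD is then unbiased and the planned model is off by (1 − b) × gap. Percentages are of the 0.20 HAZ target.

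| b | gap 0.1 | gap 0.2 | gap 0.3 |
|---|---|---|---|
| 0.6 | 0.04 (20%) | 0.08 (40%) | 0.12 (60%) |
| 0.7 | 0.03 (15%) | 0.06 (30%) | 0.09 (45%) |
| 0.8 | 0.02 (10%) | 0.04 (20%) | 0.06 (30%) |
| 0.9 | 0.01 (5%) | 0.02 (10%) | 0.03 (15%) |

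If the same gap and slope held for WAZ, the percentages would double, because its target is 0.10. For fish intake from a 24-hour survey the slope may be lower: at an assumed b of 0.3, lasting gaps of 0.1, 0.2 and 0.3 SD give 0.07, 0.14 and 0.21 SD.

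On whether such gaps are plausible: with four against four clusters, SD 1 and assumed ICC of 0.02 to 0.10, the SD of the between-group gap from village effects alone is √(2 × ICC / 4), or 0.10 to 0.22, before any matching.

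**Step 4: simulation.** 160 per group, SD 1, parallel trends built in, independent children, 1,000 runs per setting.

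- True effect 0, gap +0.2: DiD averaged −0.001 to 0.003. The planned model averaged 0.083, 0.060, 0.039 and 0.020 at correlation 0.6, 0.7, 0.8 and 0.9. Its one-sided 5% error rate was about 24%, 19%, 14% and 10%.
- True effect 0.20, correlation 0.7: with gap +0.2, DiD averaged 0.200 and the planned model 0.260. With gap −0.2, they averaged 0.197 and 0.136, and the planned model's one-sided power was 51%, against 78% with no gap.

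Clustering was ignored, so these error rates and powers only illustrate the effect of the bias.

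**Step 5: the mirror case.** If the groups are comparable given baseline, t is the true effect and DiD = true effect − (1 − b) × gap. The error has the same size and the opposite sign, and it falls on plain DiD.

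**The case against.** The strongest reply is that adjusting for baseline is defensible here. Communities are matched on child nutritional status, and the eligibility section also compares them on usual diets. This should shrink any lasting gap and makes conditioning on baseline more reasonable. Baseline adjustment also removes a share b of a lasting gap, so 60% to 90% over the range above. If part of an observed gap is measurement noise, as is likely with a single 24-hour recall, that part regresses by endline and the unadjusted change score carries the larger error. The simulation builds in parallel trends, so the near-zero bias of DiD there follows from its set-up. All of this stands. It rules out calling the planned model wrong in itself.

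The existing safeguards also count, but they do not settle the point. Matching and propensity scores act on measured differences; the DiD claim concerns what is left over.

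It can also be said that exact model terms belong in a statistical analysis plan. That would answer a missing detail. Here both the covariate and the claimed property are stated, and they do not fit together.

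A reader might infer that any baseline gap biases the planned effect, or that DiD is the only correct analysis. The protocol supports neither. The bias needs parallel trends, a lasting gap and b below 1, and nothing in the document shows which assumption holds.

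**Conclusion.** The mismatch is real for HAZ, WAZ, fish intake and dietary diversity. The model as written is ANCOVA, while the Design section claims a property that belongs to DiD. The algebra is exact for an identity link and does not depend on any assumed number.

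The size does depend on assumptions. Under parallel trends the error is 0.01 to 0.12 HAZ (5% to 60% of target) for the assumed gaps and slopes, and larger in SD units where the baseline is noisy. A higher intervention baseline inflates the effect and a lower one attenuates it. It is zero if the gap is zero or b is 1.

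The point does not extend to the binary outcomes, which use robust Poisson, or to fisheries yield and earnings, which are sampled repeatedly over 12 months; the Analysis section gives yield its own list of confounders. This should be corrected before analysis, because choosing between two reasonable estimates after seeing the data is the avoidable risk.

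**What to change.** State one estimand and its assumption in advance for the continuous nutrition outcomes, by one of two routes.

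- **Keep DiD, as the Design section says.** Fit group, time and group-by-time, or the change score without its own baseline as a covariate. Always report the baseline-adjusted model beside it.
- **Keep the baseline covariate.** Call the model ANCOVA, state that it relies on comparability given baseline, drop the DiD justification, and always report DiD beside it.

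Under either route, reword the Design claim: DiD removes only time-constant confounding, under parallel trends, and two nutrition waves cannot check those trends.

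The cost is some rewording and one extra model for each continuous nutrition outcome. The interval without baseline adjustment may be wider. The two estimates may disagree, and a disagreement should be reported with the assumption behind each.

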### Logic framework

Figure 1 illustrates the logical framework for our integrated nutrition and fisheries intervention We expect our nutrition social marketing campaign to increase consumption of fish among children under 5 and dietary diversity for households, leading to reduced enteric disease morbidities and reduced stunted growth and development. We anticipate modified fishing traps with escape gaps (to allow immature fish to leave the trap while retaining mature fish) to promote fisheries sustainability and increase fisher income, leading to greater harvest efficiency, improved resilience to environmental change, dietary diversification, and improved nutritional status through both direct consumption and indirect poverty reduction pathways.

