## Methods and analysis

### Design

We aim to test the effectiveness of the multi-component *Samaki Salama* intervention as it intersects with nutrition security and fisheries sustainability in Kilifi County, Kenya. Table 1 details the specific aims and hypotheses.

**Table 1 T1:** Study aims and hypotheses.

**Study aims**	**Hypotheses**
1. Determine the effects of a multi-component social marketing campaign to promote fish nutrition, dietary diversity, and food safety on child growth	**Primary** Hypothesis 1: Children in combined intervention groups have increased height-for-age *Z* by 0.2 compared to children in the control Hypothesis 2: Children in combined intervention groups have increased weight-for-age *Z* by 0.10 compared to children in the control Hypothesis 3: Children in combined intervention groups have increased fish food intakes by 100 g compared to children in the control
	**Secondary** Hypothesis 4: Children in combined intervention groups have increased dietary diversity by 1.2 compared to children in the control Hypothesis 5: Children in combined intervention groups have reduced diarrheal morbidity by 5 percentage points compared to children in the control
	**Exploratory** Hypothesis 6: Children in the social marketing + traps intervention group have increased dietary diversity and fish intake compared to children in the social marketing only group
2. Measure the impact of modified fishing traps with escape gaps on catch dynamics and earnings	**Primary** Hypothesis 7: Fishers in the social marketing + traps intervention group have significantly increased fisheries yields of mature fish compared to fishers in the control
	**Secondary** Hypothesis 8: Fishers in the social marketing + traps intervention group will have significantly increased earnings compared to fishers in the control

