The intervention will target communities matched based on location (rural), livelihoods, and child nutritional status. The matched sample will be divided into three groups: (1) control (*n* = 200); (2) multi-component nutrition social marketing intervention to fishers, mothers, and health workers (*n* = 100); (3) multi-component nutrition social marketing intervention plus modified fishing traps with escape gaps and training (*n* = 100). Although our original design was to have two comparison groups with equal numbers, formative research showed insufficient numbers of fishers currently using traps that could be recruited to use modified traps. Further, budgetary constraints precluded distributing traps to all 200 in the intervention group. Thus, we split the intervention group enabling us to test the added effects of modified traps together with social marketing. Figure 2 provides an overview of the study design and implementation process.

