### Participant eligibility, recruitment, and retention

At the outset of the study, we will identify comparable communities associated with BMUs on the coast of Kilifi County using potential confounding variables: proximity to shoreline or ability to participate in the fishery; presence of no-take fisheries closures; composition of fishing gears used; background nutritional status; usual diets; income and assets; and access to market information. We will draw on existing relationships and data from communities where formative research was previously conducted by the project team. BMU leaders and other stakeholders will be convened to first inform them of the potential project and solicit permission to act in partnership with BMUs to conduct the research.

To be eligible to participate in the study, an individual must meet all of the following criteria:
A household member works in small-scale fisheries (self-employed fishers).At least one child in the household aged 6–60 months.Provision of signed and dated informed consent form.For children, informed assent and parental informed consent to participate in the study.Stated willingness to comply with all study procedures and availability for the duration of the study.

An individual who meets any of the following criteria will be excluded from participation in the study:
No household member works in small-scale fisheries (self-employed fishers).No child in the household aged 6–60 months.Declines to sign the informed consent.Index child is severely malnourished.Lives outside the study area.Participation in another nutrition or fisheries intervention study within April 2021 - June 2022.

We anticipate a total sample size of 400 small-scale fisher household units (mother, father, and child 6–60 months). There will be 100 in each intervention group (social marketing and social marketing plus modified traps) and 200 in the control group. Table 2 provides a summary of the total number of individuals and anticipated demographics.

**Table 2 T2:** Sample size and demographics.

**Group 1: Control (n = 200)**			**Group 2: Social marketing (n = 100)**			**Group 3: Social marketing + modified traps (n = 100)**		
**Group**	**# of individuals**	**Anticipated sex**	**Group**	**# of individuals**	**Anticipated sex**	**Group**	**# of individuals**	**Anticipated sex**

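### Aim 1 names the effect of the social marketing campaign, but H1–H5 estimate the effect of a package in which half the households also receive traps, so a positive pooled result cannot by itself be attributed to the campaign

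*Protocol article*

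**What the plan says.** Table 1 (Design) gives Aim 1 as: "Determine the effects of a multi-component social marketing campaign to promote fish nutrition, dietary diversity, and food safety on child growth". Traps are not mentioned there; they belong to Aim 2, on catch and earnings. The five confirmatory hypotheses under Aim 1 (H1–H5: HAZ, WAZ, fish intake, dietary diversity, diarrhoea) are all worded for the pooled arms. H1, for example, begins "Children in combined intervention groups have increased height-for-age".

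The analysis section makes this a rule: "To test for intervention effectiveness, the two intervention groups will be combined for all hypotheses except" for two named cases. One is fisher earnings (H8); the other is the exploratory comparison of the two intervention arms (H6).

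On group sizes: "There will be 100 in each intervention group (social marketing and social marketing plus modified traps) and 200 in the control group". The Design section explains why there are two intervention arms: "Thus, we split the intervention group enabling us to test the added effects of modified traps together with social marketing".

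The Logic framework gives the traps their own route to child nutrition, ending in "improved nutritional status through both direct consumption and indirect poverty reduction pathways". The only listed child-level comparison of the two intervention arms is the exploratory H6, that children in the trap arm "have increased dietary diversity and fish intake compared to children in the social marketing only group".

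**The concern.** The aim and the contrast differ. The aim is about one component. The contrast averages an arm with that component alone (group 2) and an arm with that component plus traps and training (group 3). The plan cannot treat the trap contribution as negligible, because its own framework and H6 predict one.

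For HAZ, WAZ and diarrhoea, the listed hypotheses neither compare group 2 with control nor compare group 3 with group 2. If H1 is met, the listed results cannot show how much of the growth difference came from the campaign. At stake is how Aim 1 is concluded. A sentence saying that social marketing improved growth would go beyond what the pooled test estimates.

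**Working it through.** **Inputs from the article.** Control 200, group 2 100, group 3 100; HAZ effect 0.20; 20% loss; α = 0.05; power 0.80; one-tailed test (analysis section; the sample size section does not give sidedness). After loss: 160 control, 80 + 80 intervention. No SD of HAZ or HAZ change and no ICC is given, so both are assumptions below.

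**The plan's own figure.** The total of 400 can be neither confirmed nor refuted without an SD and an ICC. With 160 v 160 completers and no design effect, 80% power for 0.20 requires SD = 0.2 × √(160/2) / (z_α + z_β):
- two-sided: 1.789 / 2.802 = 0.64
- one-sided: 1.789 / 2.486 = 0.72

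**What the pooled contrast estimates.** Let C be the campaign effect and T the added effect of traps, assumed additive. Group 2 − control = C. Group 3 − control = C + T. With a 100:100 split, pooled − control = 0.5·C + 0.5·(C + T) = C + 0.5·T.

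Three different truths give the same pooled HAZ difference, equal to the H1 target:

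| C | T | C + 0.5·T |
|---|---|---|
| 0.20 | 0 | 0.20 |
| 0.10 | 0.20 | 0.20 |
| 0 | 0.40 | 0.20 |

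This does not depend on the SD or ICC.

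**Illustration with C = 0** (one-tailed 0.05, assumed SD 0.7, no clustering). Pooled SE = 0.7 × √(1/160 + 1/160) = 0.078.
- T = 0.2: pooled effect 0.10; H1 declared in about 35% of simulated trials (43% at SD 0.6, 22% at SD 1.0).
- T = 0.4: pooled effect 0.20; about 81% (90% to 55%).

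**The same with clustering.** Assume 40 completers per cluster (50 × 0.8) and ICC 0.02 to 0.05. Design effect = 1 + 39 × ICC = 1.78 to 2.95, so pooled SE = 0.078 × √DE = 0.104 to 0.134. If the analysis allows for clustering, 35% becomes about 25% to 18%, and 81% becomes about 61% to 44%. If it does not, the group 2 versus control test no longer has 5% error under C = 0; it rises to about 11% to 17%.

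**Precision of the arm-specific contrasts.**
- Group 2 v control: SE ratio to pooled = √[(1/100 + 1/200) / (1/200 + 1/200)] = √1.5 = 1.22.
- Group 3 v group 2: √[(1/100 + 1/100) / (1/200 + 1/200)] = √2 = 1.41.
- Power of group 2 v control for 0.20, before clustering: 62.8% (two-sided) or 65.0% (one-sided) at the SD that gives the pooled test 80%; about 67% against 82% pooled at SD 0.7, one-tailed.

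**The case against.** The strongest reply is that nothing is hidden. H1–H5 each say that the arms are combined, the analysis section repeats it, and the Design section opens by saying that the Samaki Salama intervention as a whole is to be tested. The pooled contrast is a valid test of the hypotheses as worded, and it keeps the planned 200 v 200 comparison after a shortage of trap fishers and budget limits forced the split. On this view one aim is worded more narrowly than its hypotheses. This stands, and it is why the pooled test should stay.

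H6 also partly covers the gap for fish intake and dietary diversity, the outcomes of H3 and H4. That stands too, but H6 is exploratory and leaves out HAZ, WAZ and diarrhoea.

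Group 2 is not a clean isolate of the campaign either. Allocation is not randomised, traps go to basket-trap fishers, and Table 4 has social marketing fishers also committing to catch more mature fish. This limits what the extra contrasts can show, but it does not make the pooled contrast a campaign estimate.

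A reader might go further and infer that the pooled test has a false-positive rate of 35% or 81% instead of 5%. The documents do not support that. They state no null hypothesis about the campaign alone, and those rates rest on an assumed SD, no clustering and a campaign effect of exactly zero; 81% also needs a trap effect of 0.4, twice the hypothesised 0.20. A reader might also infer that the campaign would be scaled alone on this result. The article says no such thing; its abstract presents the integrated approach as what would be scaled. Nor can one say that group 2 will never be compared with control, only that this is not among the listed hypotheses; a separate analysis plan may include it.

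**Conclusion.** The mismatch is real and stated in the article: Aim 1 names the campaign, while H1–H5 and the pooling rule estimate the package. Under additivity and equal arm sizes the pooled estimate carries half of any added trap effect, and the plan itself expects such an effect. A positive pooled result for any of H1–H5 therefore cannot by itself be credited to social marketing. The pooled analysis is not invalid; the fault lies in what Aim 1 says it answers, and in having no listed contrast that would support a campaign-only statement on growth or diarrhoea. The algebra is firm. The rejection rates are illustrations only, since the article gives neither SD nor ICC.

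**What to change.** 1. Keep the pooled contrast as primary, but call it and its conclusion the effect of the Samaki Salama package (campaign with or without traps). Reword Aim 1 to match.
2. Fit the same models with a three-level group term. For H1–H5, report group 2 versus control and group 3 versus group 2 as secondary estimates, with confidence intervals that account for clustering.
3. Base any statement about social marketing alone on the group 2 estimate and its interval, not on the pooled test. A significant group 2 result need not be a condition for success, given its lower power.

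The cost is wording in Table 1 and the analysis section plus two contrasts from a model already being fitted; no new data are needed. The downside is precision: the group 2 standard error is about 1.22 times the pooled one, giving about 63–67% power where the pooled test has 80–82%, before clustering lowers both. The estimate also rests on few non-randomised villages, which should be said beside it.

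### The Analysis section pools both intervention groups for primary Hypothesis 7 (yield of mature fish), whereas Table 1 defines it as social marketing + traps versus control

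*Protocol article*

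**What the plan says.** Table 1 (Design) sets out the contrasts hypothesis by hypothesis. The child outcomes, Hypotheses 1 to 5, are worded for the pooled groups; Hypothesis 1, for example, begins "Children in combined intervention groups have increased height-for-age". The second aim is to "Measure the impact of modified fishing traps with escape gaps on catch dynamics and earnings". Its one primary hypothesis, Hypothesis 7, reads "Fishers in the social marketing + traps intervention group have significantly increased fisheries yields of mature fish compared to fishers in the control". Its secondary hypothesis, Hypothesis 8, uses the same two groups: "Fishers in the social marketing + traps intervention group will have significantly increased earnings compared to fishers in the control".

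The Analysis section (Primary and secondary outcomes) then gives a general rule: "the two intervention groups will be combined for all hypotheses except the secondary outcome of increased fisher earnings", followed by a second exception, the "exploratory hypothesis for differences between social marketing and social marketing + traps intervention groups". These exceptions correspond to Hypotheses 8 and 6. Hypothesis 7 is in neither, and no other part of the article exempts it.

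The group sizes are 200 control, 100 social marketing and 100 social marketing + traps. The Design section explains the split in part by cost: "budgetary constraints precluded distributing traps to all 200 in the intervention group".

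**The concern.** Hypotheses 7 and 8 share a comparison in Table 1 and rely on the same landing-site catch survey. Under the Analysis section they would nevertheless be tested on different contrasts: earnings on trap fishers against control, and yield on a mixture of trap and non-trap fishers against control. The mixture does not answer the question that Table 1 asks. If the modified traps work and social marketing alone does little for yield, averaging in an equal number of fishers without traps weakens the estimate and the test for the only primary outcome of the second aim.

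**Working it through.** **1. The two rules side by side**

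| Hypothesis | Contrast in Table 1 | Contrast under the Analysis section |
|---|---|---|
| 1 to 5 | combined groups vs control | combined groups vs control |
| 6 (exploratory) | social marketing + traps vs social marketing | not pooled (excepted) |
| 7 (primary) | social marketing + traps vs control | combined groups vs control |
| 8 (secondary) | social marketing + traps vs control | not pooled (excepted) |

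Only Hypothesis 7 disagrees.

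**2. What pooling does to the estimate**

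Let d3 be the effect of social marketing + traps and d2 the effect of social marketing alone, each against control. With 100 fishers in each group and equal weights:

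pooled effect = (100·d3 + 100·d2)/200 = d2 + 0.5·(d3 − d2).

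The increment due to traps, d3 − d2, therefore enters at one half. As a fraction of the Hypothesis 7 effect, the pooled effect is (1 + d2/d3)/2:

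- d2 = 0: 50%
- d2 = 25% of d3: 62.5%
- d2 = 50% of d3: 75%
- d2 = 75% of d3: 87.5%

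**3. What pooling does to power (illustration)**

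There is no stated power figure for Hypothesis 7 to reproduce. The 400 households come from a calculation on height-for-age, and the article gives no effect size, SD or intracluster correlation for yield.

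Inputs:
- From the article: group sizes 100 and 200; 20% loss (Sample size section), leaving 80 and 160, and 160 when the intervention groups are pooled; one-tailed 0.05 test (Analysis section).
- Assumed: standardised effect d3 = 0.40; one independent observation per household.

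Formula: power = Φ(effect/SE − 1.645), with SE = √(1/n₁ + 1/n₂).

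- Table 1 contrast, 80 vs 160: SE = √(1/80 + 1/160) = 0.1369; 0.40/0.1369 = 2.921; Φ(1.276) ≈ 90%.
- Pooled, 160 vs 160, d2 = 0: effect 0.20; SE = √(2/160) = 0.1118; 0.20/0.1118 = 1.789; Φ(0.144) ≈ 56%.
- Pooled, d2 = 0.20 (half of d3): effect 0.30; 0.30/0.1118 = 2.683; Φ(1.038) ≈ 85%.

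**4. Break-even**

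Pooling matches the power of the Table 1 contrast when (1 + f)/2 = 0.1118/0.1369, where f = d2/d3. This gives f ≈ 0.63. Below that, pooling costs power. Above it, pooling gains power, but for a different question from Hypothesis 7.

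**The case against.** The strongest reply is that this is a drafting slip. Hypotheses 7 and 8 are worded alike, so the author of the analysis paragraph may have meant to except both fisheries hypotheses and named only one. A statistical analysis plan that is not shown may also settle it. That is plausible, but the printed rule covers all hypotheses outside its two exceptions, so the text still has to be corrected.

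Three stronger readings are tempting, and the documents do not support them.

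- A reader might infer that the Hypothesis 7 effect is exactly halved. That requires social marketing alone to have no effect on yield. Table 4 shows that social-marketing-only fishers also discuss catching mature fish and make a commitment to do so, so some effect is possible. The weights may also depart from 100:100, because catches are sampled at landing sites.
- A reader might infer that pooling is wrong because it credits traps with a social-marketing effect, and that the Table 1 contrast cures this. It does not: trap fishers receive social marketing too, so social marketing + traps versus control measures the package. Only a comparison of the two intervention groups isolates the traps, and Hypothesis 6 applies that to children's diet, not to yield.
- A reader might infer that the contrast was left open so that it could be chosen after seeing the data. The documents show two inconsistent statements and nothing about intent; Table 1 on its own is clear.

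The power figures are also fairly open to challenge. Yield comes from repeated landing-site sampling, not one independent value per household, and the 20% loss was stated for the household sample. They serve as an illustration only.

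**Conclusion.** Wrong as written. The Analysis section, followed literally, tests the only primary hypothesis of the second aim on a contrast that differs from Table 1. That conclusion rests on the text alone and needs no assumption.

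The size of the consequence does depend on assumptions. With equal weights the trap increment is counted at one half, and the full Hypothesis 7 effect is reduced by up to half. In the illustration, power falls from about 90% to somewhere between 56% and 85% as the social-marketing-only effect goes from zero to half of the full effect. Clustering would lower all of these figures, and the article gives nothing from which to say by how much.

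**What to change.** Replace the pooling sentence in the Analysis section with wording to this effect: *The two intervention groups are combined for Hypotheses 1 to 5 only; Hypotheses 7 and 8 compare social marketing + traps with control; Hypothesis 6 compares social marketing + traps with social marketing.* Add that the Hypothesis 7 result will be described as the effect of the combined package, not of the traps alone.

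If pooling for yield is really intended, Table 1 must be changed instead, since both statements cannot stand; the primary fisheries contrast would then no longer match the stated aim. The cost is a sentence or two of text, with no new data and no change to design or sample size.
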